### Clinical study endpoints

#### Primary endpoint

The primary efficacy outcome is the rate of patients presenting a pain reduction of at least two points at 9 months compared to baseline. Pain will be evaluated using a numeric scale from 0 (No pain) to 10 (Worst pain) by considering the average pain in the last 24 hours. Modification of a pain treatment strategy will be considered as a failure if the modification relates to neuropathic pain. Pain treatment modifications that are not related to neuropathic pain and missing values will not be considered as a failure.

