#### Secondary endpoints

The sensitivity endpoint is defined as the rate of patients presenting a pain reduction of at least two points at 9 months compared to baseline. Modification of the pain treatment strategy for any reason or patients with missing values will be scored as a failure*.

Neuropathic pain will be evaluated using the French language Neuropathic Pain Symptom Inventory (NPSI) which was developed and validated in that language [18]. The NPSI is a self-administered questionnaire specifically designed to evaluate the different symptoms of neuropathic pain.

Safety will be assessed using the toxicity grading of the National Cancer Institute (NCI-CTCAE v5).

Quality of life will be evaluated with the EORTC QLQ-C-30 questionnaire.

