### Sample size calculation

Based on the literature, we expect 25% of patients to present with a pain decrease of at least two points [6]. To detect a 25% improvement (i.e., standard: 25%, experimental: 50%), using a one-sided chi-square test with an alpha of 0.05%, will require the enrollment of 125 patients, for 90% power. Assuming that 5% of patients will be lost to follow-up, we will need to randomize 130 patients (Randomization ratio1:1). According to the recommendations for comparative phase II trials, the target differences and type I error rates are relaxed.

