### Main statistical analysis

The primary endpoint will be analyzed on the Intent To Treat population and expressed as values and percentages with 95% one-sided confidence intervals. Treatment effect will be estimated using a logistic regression model adjusted for stratification factors [19]. Odds ratios will be estimated with their 95% confidence intervals (one sided). The sensitivity analysis will be conducted using a similar method. Depending on the extent of missing data, the following complementary analyses may be conducted to evaluate its influence on the results of the study: case complete study, multiple imputation for missing data.

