## Discussion

As the population of head and neck cancer survivorship increases, it has become increasingly important for health care providers to propose an optimized treatment for neuropathic pain. There is an unmet need for well-designed, robust clinical trials to help improve therapeutic strategies in this setting. Single arm trials, introduce several forms of bias including patient selection, and misspecification of the hypothesis. We therefore opted for a randomized comparative phase II TEC-ORL trial design. Randomized comparative trials are an essential tool to evaluate therapeutic strategies and new treatments. However, designing and conducting a randomized trial on supportive care for neuropathic pain is associated with several challenges [20]. Several new treatments that appeared effective in phase 2 trials subsequently failed to confirm efficacy in phase 3 registration trials. This may be explained by the application of restrictive inclusion criteria in the phase 2 trial to maximize treatment effect differences, but this approach ultimately impedes the external validity, and/or generalizability of the phase 2 trial. Restricted inclusion criteria may also potentially limit the relevance of randomized controlled trial results to ‘real-world’ practices and make patient recruitment difficult [21]. The primary reason for integrative pain trial failure is inadequate patient recruitment numbers. As cancer pain management takes place in the context of multiple, sometimes competing personal interests, the primary reason for non-participation is due to the patient and/or investigator. The other challenge is the poor retention of participants in pain trials, which may lead to missing outcome data and may introduce bias and reduce study power. In this setting, there is a need for specific strategies to improve the recruitment and retention of participants in randomized trials.

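### The primary endpoint says only that a missing 9-month score is not a failure, so an ITT analysis must either count that patient as a responder or drop the patient, and the protocol does not settle which

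*Protocol article*

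**What the plan says.** - **Protocol article, Primary endpoint.** The outcome is binary: "The primary efficacy outcome is the rate of patients presenting a pain reduction of at least two points at 9 months compared to baseline". A change in pain treatment made because of neuropathic pain is a failure. The section then adds: "Pain treatment modifications that are not related to neuropathic pain and missing values will not be considered as a failure". It gives missing values no other status.
- **Main statistical analysis.** "The primary endpoint will be analyzed on the Intent To Treat population", with a logistic model adjusted for the stratification factors. On missing data: "Depending on the extent of missing data, the following complementary analyses may be conducted to evaluate its influence on the results of the study". The two analyses named are "case complete study, multiple imputation for missing data". No threshold is given for when they would be run.
- **Secondary endpoints.** The sensitivity endpoint uses the same two-point response with different rules: "Modification of the pain treatment strategy for any reason or patients with missing values will be scored as a failure". Its analysis is planned without condition.
- **Sample size calculation.** 125 patients are raised to 130 for 5% loss to follow-up. No loss rate by arm is given.
- **Follow-up.** The numeric pain score is collected every 3 months.
- **Discussion.** After recruitment, the article names as the other challenge "poor retention of participants in pain trials, which may lead to missing outcome data", with possible bias and loss of power.

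**The concern.** In a logistic model each patient is a success, a failure, or absent. Ruling out failure leaves two options: the patient is a responder, or the patient contributes nothing. The first credits a treatment with pain relief that nobody observed. The second departs from the ITT set that the same article names.

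The article supports both readings. A complete-case analysis appears only as an optional complement, which suggests that the primary analysis keeps missing patients in as non-failures. The sample size is inflated for loss, which suggests that they drop out.

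This is more than detail left to an analysis plan, because the article states a rule and the rule does not work. The trial is open-label and compares nine months of a daily oral drug with three patch applications, so attendance at 9 months could differ by arm. The answer could then depend partly on who stops attending, in either direction.

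**Working it through.** **Inputs from the Protocol article.** Response 25% (control) and 50% (patch); one-sided test; 90% power; 125 patients, 130 randomised 1:1, so 65 per arm; 5% loss overall. The alpha is printed as 0.05%. I read it as 0.05, because only that value reproduces the sample size (0.0005 would need 308). The misprint is a separate matter.

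**Assumed.** Missing rates by arm, *m*, and how missingness relates to outcome.

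**Step 1: the plan's own figure.** With pooled variance and no continuity correction,

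n per arm = [1.645·√(2·0.375·0.625) + 1.282·√(0.25·0.75 + 0.50·0.50)]² / 0.25² ≈ (1.126 + 0.848)² / 0.0625 ≈ 62.3.

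That is about 125 in total, or 126 with 63 per arm. Then 125/0.95 = 131.6, against 130 stated. The plan's figure reproduces.

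**Step 2: rates under each reading.** For true response *p* and missingness unrelated to outcome:
- missing = success: observed rate p(1 − m) + m, with 65 per arm;
- excluded: rate p, with 65(1 − m) per arm, rounded;
- missing = failure: rate p(1 − m), with 65 per arm.

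If every missing patient is a true failure, the rate is p + m under missing = success and p/(1 − m) under exclusion.

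**Step 3: rejection probabilities.** I summed the exact binomial probabilities of all outcomes in which the pooled z statistic exceeds 1.645. With nothing missing, power is 90.8%. The test is unadjusted, so it approximates the planned adjusted model.

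*Planned effect, 25% vs 50%, missingness unrelated to outcome (power):*

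| Missing, control / patch | Rates if missing = success | Missing = success | Excluded |
|---|---|---|---|
| 5% / 5% | 28.75% vs 52.5% | 86.7% | 90.3% |
| 10% / 10% | 32.5% vs 55% | 82.5% | 88.4% |
| 20% / 20% | 40% vs 60% | 73.6% | 84.7% |
| 15% / 5% | 36.25% vs 52.5% | 57.8% | 88.4% |

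*No true effect, 25% in both arms (one-sided type I error):*

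| Missing, control / patch | Missing patients are | Missing = success | Excluded |
|---|---|---|---|
| 5% / 5% | unrelated to outcome | about 5% | about 5% |
| 2.5% / 7.5% | unrelated to outcome | 12.2% (26.9% vs 30.6%) | about 5% |
| 5% / 15% | unrelated to outcome | 23.5% (28.75% vs 36.25%) | 5.3% |
| 5% / 15% | all true failures | 32.6% (30% vs 40%) | about 10% (26.3% vs 29.4%) |

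The 2.5%/7.5% row averages to the plan's 5% overall.

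**Step 4: does the sensitivity endpoint settle it?** With no true effect and 5%/15% missing unrelated to outcome, missing = failure gives rates of 23.75% vs 21.25% and a rejection rate of about 2.4%. A false positive from missing = success would therefore often show up as disagreement between the two analyses. With 15%/5% the rates are 21.25% vs 23.75% and the rejection rate is 9.7%, so this rule is not neutral either. The endpoint also turns treatment changes made for any reason into failures. If it disagrees with the primary, the cause could be either rule.

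**The case against.** A reader might infer that the plan counts missing patients as responders, and that 23.5% is its type I error. The documents do not support that. The same sentence also covers treatment changes unrelated to neuropathic pain, and there it can only mean that the patient is not failed automatically and the score decides. Read in parallel, missing values are merely not failed automatically. The inflation for loss also fits exclusion. Under exclusion the harm is much smaller, and the only documented loss rate is 5%. This stands: the large figures belong to one reading and to assumed imbalances. It does not tell an analyst what to do with a patient who has no score, and listing complete-case analysis only as a complement points the other way.

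Three further inferences go too far:
- *Everyone lost for lack of benefit is credited or removed.* Patients with a recorded treatment change for neuropathic pain are already failures. Only those who leave without one are affected.
- *The missing-as-failure analysis is optional.* It is planned; only complete-case and multiple imputation are conditional.
- *The article calls retention the main threat.* It puts recruitment first.

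Nor would exclusion make complete-case analysis an exact copy of the primary. A patient with a neuropathic-pain treatment change and no 9-month score is a failure in the primary but could be absent from an analysis of complete scores.

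It is also fair to say that imputation detail usually belongs in the analysis plan. The status of a missing outcome is different, because the article has already fixed it, and fixed it badly.

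**Conclusion.** The point holds as a defective stated rule: the endpoint, sample-size and analysis sections do not agree on what a missing 9-month score counts as in the primary ITT analysis.

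The size depends on the reading. At the plan's 5% loss split evenly and unrelated to outcome, the effect is modest (power 86.7% if missing = success, 90.3% if excluded, type I error about 5% either way). It becomes serious under missing = success once loss is unbalanced: type I error is 12.2% at 2.5%/7.5% and 23.5% at 5%/15%, and power is 57.8% at 15%/5%. Exclusion keeps type I error near 5% if missingness is unrelated to outcome, and lets it rise to about 10% at 5%/15% in the extreme case that all missing patients are true failures. All by-arm rates are assumptions.

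The planned sensitivity endpoint reduces the risk of a misleading conclusion but neither defines the primary analysis nor isolates the effect of missing data. This should be fixed; it does not invalidate the design.

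**What to change.** 1. In Primary endpoint, delete the reference to missing values from the not-a-failure sentence.
2. State one primary rule that keeps all randomised patients. One suitable option is multiple imputation of the 9-month score by arm, using the baseline, 3-month and 6-month scores, with response derived after imputation. Patients who had a neuropathic-pain treatment change stay failures whether or not a score exists. Add an explicit rule for deaths.
3. If imputation is chosen, make it unconditional in Main statistical analysis.
4. Keep missing = failure as a sensitivity analysis, but with the same treatment-modification rule as the primary, so that only one thing changes. If treating any modification as a failure is also of interest, report it separately.
5. Settle this before outcome data by arm are examined.

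Cost: wording in the endpoint and analysis sections and modest programming. No extra patients or data are needed, because the 3-monthly scores are already collected.

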#### Secondary endpoints

The sensitivity endpoint is defined as the rate of patients presenting a pain reduction of at least two points at 9 months compared to baseline. Modification of the pain treatment strategy for any reason or patients with missing values will be scored as a failure*.

Neuropathic pain will be evaluated using the French language Neuropathic Pain Symptom Inventory (NPSI) which was developed and validated in that language [18]. The NPSI is a self-administered questionnaire specifically designed to evaluate the different symptoms of neuropathic pain.

Safety will be assessed using the toxicity grading of the National Cancer Institute (NCI-CTCAE v5).

Quality of life will be evaluated with the EORTC QLQ-C-30 questionnaire.

### Randomization

After giving their written informed consent, patients which satisfy all the inclusion and non-inclusion criteria (Table 1) will be randomized by the sponsor at a 1:1 ratio to one of the two study arms. Randomization will be stratified according to: patient center, neuropathic pain at baseline (5 vs > =5), analgesic treatment at inclusion (no analgesic or neuropathic pain opioid treatment vs opioid treatment vs non-opioid treatment for neuropathic pain). A dynamic randomization procedure by minimization will be used. Randomization will be performed centrally by the IUCT-O clinical trials office using the TENALEA Clinical Trial Data Management System (online secure internet).

**Table 1 Tab1:** Inclusion and non-inclusion criteria

Inclusion Criteria	Non-Inclusion criteria
- Age ≥ 18 years. - HN cancer in remission: absence of clinical or radiological signs of progression at least 3 months after specific treatments. - Pain of the cervico-facial sphere persisting for more than 3 months after surgical and/or radiotherapy treatment. - Peripheral neuropathic character of pain objectified as a score ≥ 4/10 on the DN4 questionnaire. - Average pain intensity over the past 24 hours assessed on the numerical scale as ≥2/10. - Postmenopausal patient or patient who agrees to use effective contraception for the duration of treatment and for a minimum of 15 days after the end of the treatment period. Non-menopausal patients must have a negative pregnancy test prior to inclusion in the study. - Patient affiliated to a Social Health Insurance in France. - Patient who signed informed consent prior to inclusion in the study and prior to any specific study procedures.	- HN cancer progression. - Other concomitant neoplasia (progressive or not). - Central pain etiology. - Average pain intensity over the past 24 hours is assessed on the numerical scale as < 2/10. - Allergy to any of the components of the capsaicin patch. - Capsaicin patch cannot be applied to the area to be treated despite taking the precautions described in the protocol because of proximity to mucous membranes or eyelids. - Contraindication of amitriptyline treatment. - Patient with an unhealed skin lesion on the area to be treated. - Previous course of capsaicin or amitriptyline treatment. - Topical treatment of the painful area used for more than 21 days before inclusion. - Ongoing opioid treatment > 80 mg/day oral morphine equivalent. - Uncontrolled high blood pressure or cardiovascular history (infarction, stroke, pulmonary embolism) less than 3 months ago. - Patient included in another interventional therapeutic trial. - Pregnant or breastfeeding patient. - Any psychological, family, geographical or sociological condition that prevents compliance with the medical follow-up and/or procedures of the study protocol. - Patient who has forfeited his/her freedom through an administrative or judicial sentence or who is under legal custody (curatorship and guardianship, protection of justice).

### Treatment

#### Standard of care

Patients randomized to the control arm will be treated with Amitriptyline (Laroxyl®) (oral solution 40 mg/ml) taken for 9 months at the recommended daily dose of 25 mg to 75 mg.

#### Experimental treatment

Patients randomized to the experimental arm will be treated by application of an 8% capsaicin patch (Qutenza®) at three time intervals: the first application within two weeks of randomization and the next two applications at three monthly intervals.

### Follow-up

Patients will be followed-up every 3 months from the date of randomization. Assessments will include, clinical examination, pain evaluation using the numeric scale (primary endpoint), quality of life evaluation based on the EORTC QLQ-C30 questionnaire and neuropathic pain evaluation with the NPSI. Any adverse events (AE) related to the study treatments will be collected until completion of the study.

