#### Secondary objectives

Secondary objectives include a sensitivity analysis, the evolution of neuropathic pain, the safety and health related quality of life.

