### Trial design

This is a Phase II, multicenter, randomized open-label and comparative study designed to evaluate whether Capsaïcin patches (Qutenza®) reduce neuropathic pain when compared to Amitriptyline (Laroxyl®) in head and neck cancer survivors presenting with neuropathic pain sequelae (ClinicalTrials.gov Identifier: NCT04704453). The primary endpoint is pain evaluated using a numeric scale. We opted for a randomized comparative phase II trial design rather than a single arm or a randomized non-comparative phase II trial to avoid obtaining false positive or false negative results only related to the study hypothesis [17]. All head and neck cancer patients presenting with neuropathic pain sequelae will be eligible for inclusion into the study. Patients that give their informed consent will be enrolled and randomized into the Amitriptyline (Laroxyl®) or Capsaïcin patch (Qutenza®) arm of the study.

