#### Data collection

Patient data will be collected by the investigator (or representatives) via an electronic Care Report Form (e-CRF) provided by the Institut Claudius Regaud Data Management Department. The e-CRF is based on ENNOV Clinical® software edited by Ennov Company. It is available on the secure website. Study data validation will be carried out to verify the completeness, the accuracy and consistency of data collected in the e-CRF. Data clarification forms will be issued by the Data Management Department of ICR in order to allow investigators sites to resolve data deficiencies and/or in accuracy.

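### As written, adverse events are collected only if related to treatment; in an open-label trial this leaves the safety summary by arm open to attribution bias

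*Protocol article*

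**What the plan says.** The collection rule is the last sentence of the Follow-up section: "Any adverse events (AE) related to the study treatments will be collected until completion of the study". No other section gives a rule for which adverse events are recorded.

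The surrounding design is stated as follows:

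- **Blinding.** Under Trial design: "This is a Phase II, multicenter, randomized open-label and comparative study".
- **Role of safety.** Under Secondary objectives: "Secondary objectives include a sensitivity analysis, the evolution of neuropathic pain, the safety and health related quality of life".
- **Safety endpoint.** Under Secondary endpoints: "Safety will be assessed using the toxicity grading of the National Cancer Institute (NCI-CTCAE v5". No causality limit is attached.
- **Who records.** Under Data collection: "Patient data will be collected by the investigator (or representatives) via an electronic Care Report Form (e-CRF". No blinded or independent causality review is described.
- **Treatments.** The control arm takes an oral solution daily for 9 months (Standard of care). The experimental arm receives three patch applications (Experimental treatment).

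**The concern.** Relatedness is a judgement. Here it is made by people who know which treatment the patient received, and it is made before the event is recorded. The two treatments differ in kind, one local and one systemic, so different expectations about what each can cause are plausible. A skin event may be more readily ascribed to the patch and a systemic event to the oral drug.

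Two things are at stake. First, a summary of events by arm may reflect expectation as well as occurrence. Second, an event that nobody links to treatment does not meet the stated condition for collection. The second matters because the Background says the patches are not recommended for head and neck pain, and the Discussion describes the trial as the first of its kind to the authors' knowledge. An analysis plan cannot repair either problem if the events were not recorded.

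**Working it through.** **1. Reading the text.** The safety endpoint is defined by CTCAE grading without reference to cause. The Follow-up rule admits events related to study treatment. The second statement therefore narrows the first, and no other section widens it again.

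**2. The plan's own figures.** The article gives no adverse event rate, no attribution probability and no sample size for safety, so there is no stated figure to reproduce. What follows shows the mechanism under assumptions and does not estimate an effect in this trial.

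**3. Formula.** Let t be the true event rate, equal in both arms, and let a1 and a2 be the probabilities that an event is judged related in each arm. The recorded rates are t × a1 and t × a2. The spurious difference is t × (a1 − a2).

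**4. Assumed t = 30%.**

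| Attribution (a1 vs a2) | Recorded rates | Spurious difference |
|---|---|---|
| Equal, e.g. 60% vs 60% | 0.30 × 0.60 = 18% in both | 0 points |
| 60% vs 40% | 18% vs 0.30 × 0.40 = 12% | 6 points |
| 80% vs 20% | 0.30 × 0.80 = 24% vs 0.30 × 0.20 = 6% | 18 points |

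The first row shows that equal attribution removes the false difference but still understates incidence (18% recorded against 30% true).

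**5. Other assumed values.** With a1 = 90% and a2 = 70% or 50%:

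| True rate | 90% vs 70% | 90% vs 50% |
|---|---|---|
| 20% | 18% vs 14% (4 points) | 18% vs 10% (8 points) |
| 40% | 36% vs 28% (8 points) | 36% vs 20% (16 points) |
| 60% | 54% vs 42% (12 points) | 54% vs 30% (24 points) |

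With 130 / 2 = 65 patients per arm, a nominal two-sided 5% test on the recorded rates would show a difference, although none exists, with probability from about 9% (18% vs 14%) to about 80% (54% vs 30%). With equal attribution that probability stays at 5%.

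**6. Direction.** Exchanging a1 and a2 reverses the sign. Nothing in the documents says which arm would have the higher attribution, and it may differ by type of event.

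**The case against.** The sentence does not contain the word *only*. It could be a rule about duration: related events are pursued to the end of the study, while the wider collection rule sits in the full protocol, which is not shown. A journal article condenses, and the e-CRF cannot be seen. This stands as a caution: nobody can say from the article what the database will hold. It does not remove the point. The sentence states a condition for collection, that is its natural reading, and nothing else in the article supports the duration reading. If duration was meant, the sentence still needs correcting.

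A reader might go further and infer that the safety comparison is biased, with the same event recorded in one arm and dropped in the other. The documents do not support that. They give no event or attribution rates, and equal attribution produces no spurious difference. The 80% against 20% case is an extreme choice.

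A reader might also infer that the known hazards of applying the patch to the face and neck would be missed. The Background names erythema, pain and irritation. An investigator would readily call these related, so the rule would capture them. The gap concerns unsuspected harm.

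Finally, the Main statistical analysis section covers the primary endpoint and its sensitivity version, and states no test of safety between arms. That is correct. However, a randomised comparative trial with safety as an objective can be expected to report events by arm, and a descriptive table is open to the same distortion as a test.

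**Conclusion.** The point holds in a limited form. As written, the Follow-up section restricts collection to related adverse events. In an open-label trial with safety as a secondary endpoint, this leaves any between-arm summary open to differential attribution bias, and unsuspected harms may go unrecorded. Size and direction are unknown. The 0, 6 and 18 points rest wholly on an assumed 30% true rate and assumed attribution probabilities. The conclusion also assumes that the sentence is followed as printed and that no fuller rule in the unseen protocol overrides it. This point does not affect the primary endpoint analysis. The change should be made because the filter acts at data collection, where analysis cannot undo it.

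**What to change.** Replace the sentence in Follow-up with a rule that all adverse events, regardless of causality, are collected and graded with CTCAE v5 in both arms, over the same period from randomisation to the end of follow-up. Record relatedness as an attribute of each event. Summarise all events by arm and show related events separately. If the full protocol already collects all events, correct the article's sentence to say so.

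The cost is a wording change in the protocol and e-CRF, plus some extra entry of unrelated events. Patients are already examined every 3 months, so no visit is added.
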